**Methods/Design:**

Thromboprophylaxis in Children treated for Acute Lymphoblastic Leukemia with Low-molecular-weight heparin (TropicALL) is a multicenter, randomized controlled open-label trial conducted in the Netherlands. Patients between 1 and 19 years of age with primary ALL, who are treated within the Dutch Childhood Oncology Group (DCOG) ALL-11 or 12 study will be randomized to thromboprophylaxis with LMWH once daily, (dose of 85 IU/kg (intervention arm A)), or to no thromboprophylaxis (arm B, standard of care) during asparaginase courses of ALL treatment. Primary efficacy endpoint is symptomatic objectified VTE during ALL treatment; secondary efficacy endpoints are overall survival and the composite of symptomatic and asymptomatic objectified VTE. Primary safety endpoints are major bleeding, clinically relevant non-major bleeding and minor bleeding. A total of 324 patients will be included to obtain a relative risk reduction of 75% with a power of 80%, using a two-sided test with significance level α = 0.05.

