## Methods

### Aim and study design

The TropicALL study is a multicenter randomized controlled open-label trial conducted in the Netherlands. The aim of this study is to assess the efficacy and safety of thromboprophylaxis with LMWH in children treated for primary ALL in the DCOG ALL-11 or subsequent study. As a secondary objective, clinical risk factors will be evaluated to increase insight in the pathogenesis of VTE during ALL treatment and to establish a risk model for these complications. In addition, since a thrombophilic state is associated with a higher VTE risk, specific coagulation assays, including antithrombin, fibrinogen, D-dimer, thrombin antithrombin complex (TAT) and thrombin generation, and genetic thrombophilic mutations Factor V Leiden and prothrombin G20210A will be performed in patients with and without VTE. The inclusion period is 3 years with a follow-up of 3 months after the end of the ALL treatment period, or until recurrence of ALL, or until death. Primary efficacy endpoint is the incidence of symptomatic objectified VTE during ALL treatment; secondary efficacy endpoints are incidence of the composite of symptomatic and asymptomatic objectified VTE, and the value of plasma coagulation assays to predict the risk of VTE. Primary safety endpoint is major bleeding. Secondary safety endpoints are the incidence of clinically relevant non-major bleeding and minor bleeding, the burden of LMWH injections, and adverse skin reactions.

Patients will be closely monitored for adverse events during the study. All serious adverse events and unexpected adverse reactions, will be reported through the web portal ToetsingOnline to the accredited Ethics Committee that approved the study protocol. Furthermore a Data Monitoring Committee will semi-annually review all incidences of adverse events, symptomatic VTE and bleeding complications. To enhance safety of the study, DMC will provide the core committee with recommendations related to the protection of the patients’ safety, including stopping recruitment and study treatment.

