### Treatment arms in TropicALL

All patients randomized to arm A will receive LMWH from the day asparaginase is started, until 28 days (for PEG-asparaginase) after the end of asparaginase therapy, in all treatment cycles with asparaginase (Induction cycle, Intensification in Medium Risk protocol). In case PEG-asparaginase is replaced by Erwinia asparaginase, LMWH will be given until 7 days after the last administration of Erwinia asparaginase. Patients treated according the medium risk arm of the protocol will receive 34 weeks (=238 days) of LMWH in the induction and intensification cycles, while patients treated according to the standard risk and high risk ALL-11 protocols will receive LMWH in the induction cycle only (=42 days during and after asparaginase). Patients in arm B, the standard of care arm, will not receive any form of thromboprophylaxis.

LMWH should be stopped 24 h before interventions, i.e. lumbar puncture or CVC insertion, and should be restarted after invasive procedures or surgical interventions within 24 h, provided the clinical situation allows. Moreover, LMWH should be temporarily interrupted if platelet levels drop below 20 × 10^9^/L, and in case of major bleeding.

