### Reporting of symptomatic VTE events

Patients are monitored for clinical symptoms of VTE during all treatment cycles of ALL-11 and a 3-month follow-up period. To establish systematic registration of symptomatic VTE, events must be prospectively centrally recorded on special VTE reporting forms in the CRF. VTE reporting forms include several specifications of the VTE to enable complete analysis of the event and its consequences for the patient and ALL treatment. For each symptomatic, objectively diagnosed VTE event in a study patient, a VTE reporting form should be completed and returned to the DCOG Office within 14 days after the event. Recurrent VTE should also be recorded.

Presence, replacement, removal or reinsertion of a CVC should be documented in the CRF, as well as the applied method of catheter flushing.

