### Statistical analysis

All data will be analyzed according to the intention-to-treat principle. Descriptive data will be presented as mean with its corresponding standard deviation if normally distributed, and medians with ranges if data are skewed. Depending on the data distribution the Student’s *t* test or a Mann-Whitney U-test will be used to compare continuous variables between the treatment groups. Categorical variables will be analyzed using the Chi-square test.

Efficacy and safety of LMWH to prevent VTE will be analyzed by the difference between the incidence proportions and cumulative incidences of the primary efficacy and safety outcomes, symptomatic objectified VTE and major or clinically relevant non-major bleeding, respectively, observed from randomization up to 14 and 7 days after the last PEG asparaginase and Erwinia asparaginase, respectively. A two-sided test with significance level α = 0.05 will be used.

All bleeding events that occur during LMWH or within 2 days after cessation of LMWH will be included. Incidence proportions (number of children with outcome during the period divided by number of children at risk at the beginning of the period) and cumulative incidences will be estimated by a joint model to estimate event free survival for the primary safety outcome. To identify which risks factors are associated with time to VTE a joint model for longitudinal data and survival outcome will be used.

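### The primary efficacy endpoint is defined over the whole of ALL treatment but analysed only to 14 days (PEG-asparaginase) or 7 days (Erwinia) after the last asparaginase

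*Protocol article*

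**What the plan says.** **Definition.** The abstract (Methods/Design) says "Primary efficacy endpoint is symptomatic objectified VTE during ALL treatment". The Aim and study design section says the same: "Primary efficacy endpoint is the incidence of symptomatic objectified VTE during ALL treatment".

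**Analysis.** The Statistical analysis section compares the arms on the primary efficacy and safety outcomes, naming symptomatic objectified VTE as the efficacy outcome, "observed from randomization up to 14 and 7 days after the last PEG asparaginase and Erwinia asparaginase, respectively".

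**Collection.** The section on reporting of VTE goes further than either: "Patients are monitored for clinical symptoms of VTE during all treatment cycles of ALL-11 and a 3-month follow-up period".

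**Intervention period.** The Treatment arms section continues LMWH in arm A "until 28 days (for PEG-asparaginase) after the end of asparaginase therapy". For Erwinia, "LMWH will be given until 7 days after the last administration of Erwinia asparaginase". It also prints totals. Medium-risk patients "will receive 34 weeks (=238 days) of LMWH in the induction and intensification cycles". Standard- and high-risk patients "will receive LMWH in the induction cycle only (=42 days during and after asparaginase").

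**Planning rate.** The Sample size section takes a 10% symptomatic VTE incidence from the preceding DCOG study and a 75% relative risk reduction. It does not say which period the 10% covers.

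**The concern.** VTE over all of ALL treatment and VTE around asparaginase exposure are different quantities. The first includes long stretches in which neither arm receives prophylaxis. The second concentrates on the period in which LMWH could act. They will generally give different event counts, control rates and relative risks. As written, the analysis does not estimate the endpoint that the article defines.

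Two things are at stake. A reader of the results could not tell which of the two the primary result answers. And the power calculation is tied to a 10% rate that may belong to either period.

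This is not a matter of detail left to an unseen analysis plan: the article states both periods, and they differ.

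**Working it through.** **1. The periods side by side**

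| Source in the article | VTE period |
|---|---|
| Abstract; Aim and study design | all of ALL treatment |
| Statistical analysis | randomization to 14 days after last PEG-asparaginase, or 7 days after last Erwinia |
| Reporting of symptomatic VTE events | all treatment cycles plus 3 months (collection) |

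The first two concern the same primary outcome and cannot both be its period. The third shows that the events needed for either are recorded. The separate bleeding rule in Statistical analysis (during LMWH or within 2 days after) does not extend the VTE window.

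**2. When the window closes for induction-only asparaginase**

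Inputs: randomization on day 11 (Randomization section); induction PEG-asparaginase on days 12, 26 and a third day printed as 4, read here as day 40 (assumption).

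- Window closes: 40 + 14 = day 54.
- Length from randomization: 54 − 11 = 43 days.

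All later treatment of such a child lies outside the window. The exact day depends on the assumption; the exclusion of later treatment does not.

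**3. Does LMWH run past the window?**

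Under the written 28-day rule, days 15 to 28 after the last PEG dose are LMWH days outside the VTE window. For Erwinia both limits are 7 days, so nothing is lost. The printed totals can be tested against each tail, with doses 14 days apart and 14 intensification doses:

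- Induction, last dose day 40: (40 − 12) + 14 = 42 days with a 14-day tail; 28 + 28 = 56 with a 28-day tail. Printed: 42.
- Medium risk: 42 + 13×14 + 14 = 238 with 14-day tails; 56 + 13×14 + 28 = 266 with 28-day tails. Printed: 238.
- If the last induction dose were day 26, a 28-day tail would also give 14 + 28 = 42, but the medium-risk total would then be 42 + 13×14 + 28 = 252, not 238.

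So on the day-40 reading the totals fit a 14-day tail, and LMWH would end where the window ends. The 28-day rule and the totals contradict each other.

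**4. The plan's sample size**

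Inputs: p1 = 0.10, p2 = 0.025, two-sided α = 0.05, power 80%, pooled mean p̄ = 0.0625.

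n = [1.96·√(2p̄(1−p̄)) + 0.8416·√(p1(1−p1) + p2(1−p2))]² / (p1−p2)²
= [1.96·√0.1172 + 0.8416·√0.1144]² / 0.005625 ≈ 162.3 per arm.

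This reproduces the stated 162 (163 when rounded up). Power at 162 per arm is 79.9%. The calculation is sound for whichever period the 10% describes.

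**5. What the choice of period could do to power**

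Let f be the share of control-arm VTE that falls inside the analysis window. The documents do not give f, so a range is assumed. In both cases 10% is taken as the whole-treatment rate and n = 162 per arm.

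- Case A, only the window is counted and the reduction stays 75%: control 0.10·f, LMWH 0.025·f.
- Case B, all of treatment is counted and LMWH has no effect outside the window: control 0.10, LMWH 0.10·(0.25f + 1 − f).

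| f | A: rates | A: power (n per arm for 80%) | B: rates (reduction) | B: power (n per arm for 80%) |
|---|---|---|---|---|
| 0.9 | 9.0% v 2.25% | 75.3% (182) | 10% v 3.25% (67.5%) | 68.7% (212) |
| 0.8 | 8.0% v 2.0% | 69.9% (206) | 10% v 4.0% (60%) | 56.3% (283) |
| 0.7 | 7.0% v 1.75% | 63.8% (238) | 10% v 4.75% (52.5%) | 43.9% (388) |

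If the 10% already refers to the window and the window is what is analysed, the stated power stands.

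**The case against.** The best defence is that Statistical analysis is the only section that specifies an analysis, and it fixes one window. On that view the phrase used elsewhere is a loose label, and following VTE beyond the primary window is ordinary practice. Part of this stands. The longer collection period is not itself a contradiction, and the article does not leave the analyst a free choice of window. But the looser wording is how the endpoint is formally defined, in two places, and nothing marks it as shorthand.

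Some stronger readings are tempting and are not supported:

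- **A reader might infer that VTE under LMWH certainly goes uncounted.** That follows from the 28-day rule alone. The totals of 42 and 238 days, in the same section, fit a tail with no uncounted LMWH day on the day-40 reading. The inference is conditional.
- **A reader might infer a breach of intention-to-treat, with the window shortened differently by arm.** Intention-to-treat governs the arm in which a child is analysed, and a limited window does not by itself violate it. The article does not say whether the last dose means scheduled or received, and nowhere says that LMWH or bleeding shortens asparaginase. The ambiguity should be closed, but bias is not shown.
- **A reader might infer that a single event decides the result.** With 162 per arm, 16 v 6 gives p = 0.027 and 16 v 7 gives p = 0.052 (uncorrected chi-square). But the design expects about 16 v 4, p = 0.0056, and a longer window would be expected to add events to both arms: 18 v 6 gives p = 0.011. Flipping near 0.05 is a property of any trial at the threshold. With no event timing in the documents, it does not measure the effect of the window.

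**Conclusion.** The point holds: the plan is wrong as written. One primary endpoint carries two incompatible periods, and VTE after the analysis window but during ALL treatment satisfies the definition while being excluded from the analysis. This needs no assumption.

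The size cannot be fixed from the documents, because the timing of VTE is not given. The assumed range of 70 to 90% of events inside the window gives power of 64 to 75% (window counted) or 44 to 69% (all of treatment counted, no effect outside the window), if the 10% is a whole-treatment rate. These figures illustrate how much the choice matters; they are not estimates for this trial.

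Loss of events on LMWH is only a possibility: up to 14 days after the last PEG-asparaginase if the 28-day rule applies, and none for Erwinia. Which LMWH duration applies is for the sponsor to state.

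**What to change.** 1. State one primary VTE observation period, the same for both arms, and word it identically in the abstract, in Aim and study design and in Statistical analysis.
2. In Sample size calculation, say which period the 10% control rate covers.
3. If the chosen period depends on asparaginase, say whether the last dose means the scheduled or the received one. Protocol-scheduled dates are preferable where they exist; an unscheduled switch to Erwinia needs its own stated rule.
4. Report the other period as a named secondary analysis.
5. Separately, have the sponsor reconcile the 28-day LMWH rule, the 42- and 238-day totals, the third induction dose day and the analysis window. The VTE period should not be anchored to the LMWH tail while that tail is unsettled.

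The cost is wording, since VTE is already recorded through all cycles and 3 months beyond. The downside is that, if the 10% belongs to the period not chosen, the expected event rate and the stated 80% power must be restated.

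### The bleeding analysis has two unreconciled counting windows, and one is tied to LMWH dates that the no-LMWH arm does not have

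*Protocol article*

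**What the plan says.** The Statistical analysis section of the protocol article gives two rules for which bleeding events count.

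- **Common window.** The arms are compared on symptomatic VTE and on major or clinically relevant non-major bleeding, "observed from randomization up to 14 and 7 days after the last PEG asparaginase and Erwinia asparaginase, respectively". Both arms have these dates.
- **LMWH-anchored rule.** The next paragraph opens with "All bleeding events that occur during LMWH or within 2 days after cessation of LMWH will be included" and goes straight on to how incidence proportions and cumulative incidences are estimated for the primary safety outcome. The rule is not labelled as descriptive or as limited to arm A.

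The same section begins: "All data will be analyzed according to the intention-to-treat principle".

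The section Treatment arms in TropicALL supplies the LMWH dates. Arm A receives LMWH from the start of asparaginase "until 28 days (for PEG-asparaginase) after the end of asparaginase therapy". With Erwinia, "LMWH will be given until 7 days after the last administration of Erwinia asparaginase". For the control arm, "Patients in arm B, the standard of care arm, will not receive any form of thromboprophylaxis". No substitute dates are given for arm B.

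**The concern.** A rule anchored to LMWH exposure cannot be applied to an arm without LMWH. The text leaves open whether the rule extends, restricts or replaces the common window, and each choice treats the arms differently.

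Extending the window gives arm A more observed time and would overstate bleeding on LMWH. Restricting it in arm A alone would remove arm A bleeds in LMWH-free time while arm B bleeds in the same calendar time still count, and this could understate the harm. The direction of the bias therefore depends on a choice that the plan does not make.

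Safety is half of the stated aim, and the Aim and study design section names major bleeding as the primary safety endpoint. The trial is open-label, so a window settled after events are known would be open to challenge.

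**Working it through.** **Inputs**

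| Input | Value | Section of the protocol article |
|---|---|---|
| Randomization | day 11 | Randomization |
| First PEG-asparaginase in induction | day 12 | ALL-11 study design |
| Later PEG-asparaginase in induction | day 26, and a third day printed as 4 | ALL-11 study design |
| End of LMWH after PEG / Erwinia | 28 / 7 days | Treatment arms in TropicALL |
| LMWH days, standard and high risk | 42 | Treatment arms in TropicALL |
| LMWH days, medium risk | 238 | Treatment arms in TropicALL |
| End of common window after PEG / Erwinia | 14 / 7 days | Statistical analysis |
| Tail of LMWH-anchored rule | 2 days | Statistical analysis |

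**The plan's own figure.** Standard- and high-risk children are to receive "LMWH in the induction cycle only (=42 days during and after asparaginase". With the last dose on day 26, LMWH runs for 26 + 28 − 12 = 42 days, which matches. With the last dose on day 40 (one possible reading of the printed 4), it runs for 40 + 28 − 12 = 56 days, which does not. The dosing days and the LMWH duration need to be reconciled in the protocol. Both cases are carried below as assumptions.

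**Reading 1: the LMWH rule extends the common window**

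- After PEG-asparaginase, arm A is counted to 28 + 2 = 30 days and arm B to 14 days, a difference of 16 days.
- After Erwinia, arm A is counted to 7 + 2 = 9 days and arm B to 7 days, a difference of 2 days.

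Counted time from randomization in induction-only children, taking the induction doses as their last asparaginase:

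| Last PEG dose | Arm A | Arm B | Ratio of time |
|---|---|---|---|
| Day 26 | 26 + 30 − 11 = 45 days | 26 + 14 − 11 = 29 days | 45/29 = 1.55 |
| Day 40 | 40 + 30 − 11 = 59 days | 40 + 14 − 11 = 43 days | 59/43 = 1.37 |

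To turn time into risk, assume the same constant bleeding hazard in both arms and an arm B risk *r* over its own window. Arm A risk is then 1 − (1 − *r*)^(A days / B days). The documents give no expected bleeding rate, so *r* is varied from 1% to 10%:

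- Last dose day 26: the apparent risk ratio runs from 1.55 (*r* = 1%) to 1.51 (*r* = 10%).
- Last dose day 40: it runs from 1.37 to 1.35.

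These ratios arise with no effect of LMWH at all.

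In medium-risk children, the common window contains at least 1 + (238 − 14) = 225 days, before the LMWH-free gap between induction and intensification is added. The excess is therefore at most 16/225 = 7.1%.

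**Reading 2: the LMWH rule restricts the count**

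- Applied to both arms, arm B has no countable time as planned, and no comparison is defined.
- Applied to arm A alone, arm A bleeds outside LMWH plus 2 days are dropped while arm B bleeds at the same point in treatment are kept. The clearest such period is the medium-risk gap between induction and intensification. Platelet-triggered interruptions ("LMWH should be temporarily interrupted if platelet levels drop below 20" × 10⁹/L) would join it if they last more than 2 days and if an interruption counts as cessation, which the text does not settle.

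**Sample size.** The plan's 162 per arm rests on VTE at 10% against 2.5%. The standard two-proportion formula gives 163 per arm, and 162 gives 79.9% power. The bleeding window does not enter this calculation.

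**The case against.** The strongest reply is that a common window is already there. The LMWH sentence says that such events will be included. It does not say that others are excluded, and the preceding paragraph gives both arms dates that run from randomization. A reader might infer that bleeding is counted only on LMWH, so that arm B contributes nothing; the documents do not support that as the plan's stated rule. It follows only under one restrictive reading. What remains is that the second rule changes the count in some way, and the text does not say how.

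Three other inferences also go too far:

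- **A 37% or 55% excess across the trial.** Those figures apply to induction-only children under the extending reading. Medium-risk children are 70% of patients, and their excess is at most about 7%.
- **Intention to treat is broken on any reading.** Under the extending reading children are still analysed as randomized; the defect is unequal observation time. The conflict with intention to treat arises under the restrictive reading.
- **LMWH interruptions hide bleeds in general.** A child whose LMWH is interrupted for major bleeding already has the event, and the plan counts children with the outcome. The platelet trigger matters only under the restrictive reading, and only if interruption means cessation.

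It could also be said that a condensed article leaves such detail to the full protocol. That would excuse a missing rule. Here the article states two rules that do not fit together.

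**Conclusion.** The point holds as an unreconciled pair of bleeding windows, one of them undefined in arm B. It should be fixed before the bleeding data are analysed, but it does not undermine the trial, because a randomization-based window already exists and the remedy is a matter of wording.

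The contradiction itself needs no assumption. Its size does: the 37% to 55% excess assumes the extending reading, full planned LMWH duration, an equal hazard in both arms and a last induction dose on day 40 or day 26 respectively. The limit of about 7% in medium-risk children takes the stated 238 LMWH days as including the 28-day tail after the last PEG-asparaginase. Under the restrictive reading no size can be given, since the documents report neither bleeding rates nor the amount of LMWH-free time.

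**What to change.** State one primary bleeding comparison, by randomized arm, over a window that is identical in both arms and anchored to the asparaginase schedule. It should start at randomization and include LMWH-free time.

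Using the VTE window unchanged would not be enough: it ends 14 days after the last PEG-asparaginase, while planned LMWH continues to day 28, so bleeds on LMWH in between would be lost. The end date should cover the planned LMWH period plus 2 days. On the durations now in Treatment arms in TropicALL, that is 30 days after the last PEG-asparaginase and 9 days after the last Erwinia asparaginase. If those durations change when the treatment passages are reconciled, the end date should follow them.

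Keep the LMWH-plus-2-days count as a descriptive on-treatment rate in arm A, labelled as such, and say there whether a temporary interruption counts as cessation.

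The cost is a few sentences of protocol or SAP text. The longer window falls within the planned follow-up to 3 months after ALL treatment for children who remain in follow-up, but the team should confirm that bleeding is recorded in the same way in both arms throughout. The bleeding and VTE windows will then differ, which should be stated as intended. Counting LMWH-free time slightly dilutes the on-drug bleeding rate; the arm A description recovers it. The planned 324 patients are unaffected.

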### Definitions

Symptomatic VTE is defined as suspicion of VTE based on clinical symptoms, for instance for (CVC-associated) DVT: peripheral deep vein thrombosis, swelling, erythema, skin discoloration, increased warmth, pain, tenderness, venous distension, or presence of subcutaneous collateral veins and objectively confirmed by imaging tests. Other forms of VTE (i.e. pulmonary emboli and CSVT) are defined as symptomatic venous thrombosis in any component of the venous or pulmonary arterial circulations or the heart, or the cerebral sinovenous system, requiring therapeutic anticoagulation, acute intervention, life-saving measures, ALL treatment adjustments, or of fatal nature, and objectively confirmed by routine imaging tests. Screening for asymptomatic VTE should not be performed. However, if thrombi are incidentally found upon diagnostic imaging for other indications, these are counted as asymptomatic VTE. Treatment of these asymptomatic VTE will be determined by the attending physician.

Bleeding is categorized as major, clinically relevant non-major or minor bleeding according to Perinatal and Pediatric Subcommittee of the Scientific and Standardization Committee of the International Society on Thrombosis and Haemostasis criteria [27]. A bleeding is considered as major if it is a fatal bleeding, clinically overt bleeding associated with a decrease in hemoglobin of at least 3.1 mmol/l in a 24-h period, bleeding that is retroperitoneal, pulmonary, intracranial, or otherwise involves the central nervous system; and bleeding that requires surgical intervention in an operating suite. A clinical relevant non-major bleeding is defined as an overt bleeding for which a blood product is administered and not directly attributable to the patient’s underlying medical condition or a bleeding that requires medical or surgical intervention to restore hemostasis, not in an operating suite. All other overt bleedings or macroscopic evidence of bleeding are considered minor.

Burden of LMWH injections is estimated by a visual analogue scale (VAS) score and defined as a VAS score > 5.

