### Sample size calculation

Power calculations were based on an estimated symptomatic VTE incidence of 10% based on the previous DCOG ALL-10 study, and an estimated relative risk reduction (RRR) of 75% based on the abovementioned cohort studies with LMWH in childhood ALL [25, 26, 30, 31]. Using nQuery Advisor (7.0, 2007), it was calculated that 162 patients are required in each arm for a power of 80%, using a two-sided test with significance level α = 0.05. Hence, 324 patients will be randomized in this study.

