### Withdrawal of patients

Children can discontinue their participation in the study at any time for any reason if they wish to do so without any consequences for their care, at their own request or at the request of their parents/legally acceptable representative. Furthermore, study medication can be stopped prematurely in case of serious adverse events, VTE requiring therapeutic anticoagulant treatment, or if, in the investigator’s opinion, study medication should be stopped for any other reason.

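### Two unreconciled bleeding windows: one sets no period for untreated controls, the other counts bleeds that follow a VTE as primary safety events and can dilute a prophylaxis excess

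*Protocol article*

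**What the plan says.** The Statistical analysis section of the protocol article analyses everything by intention to treat. It compares the arms on symptomatic VTE and on major or clinically relevant non-major bleeding, "observed from randomization up to 14 and 7 days after the last PEG asparaginase and Erwinia asparaginase, respectively". The next paragraph gives a second rule: "All bleeding events that occur during LMWH or within 2 days after cessation of LMWH will be included". The text does not say whether this rule replaces the first window, extends it or describes a separate count.

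The Definitions section lists among major bleeds any "bleeding that is retroperitoneal, pulmonary, intracranial, or otherwise involves the central nervous system", without regard to cause. The only exclusion by cause sits in the blood-product limb of clinically relevant non-major bleeding, and it refers to the underlying medical condition.

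Withdrawal of patients states that "study medication can be stopped prematurely in case of serious adverse events, VTE requiring therapeutic anticoagulant treatment", so anticoagulation for an established VTE is foreseen during follow-up. No section ends bleeding follow-up at a VTE or separates bleeds that come at or after one. Treatment arms in TropicALL gives arm B no thromboprophylaxis.

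**The concern.** The two windows answer different questions.

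- **The on-LMWH window** has no start or end for an arm B child, who receives no study LMWH. Read literally, it counts arm B bleeds only while LMWH is being given to treat a VTE.
- **The randomization-based window** applies to both arms but pools two kinds of bleed: those that prophylaxis may cause, and those that arise from a VTE or its treatment. An effective drug prevents VTEs, so the second kind should fall mainly in arm B.

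The Background describes the bleeding risk on LMWH as negligible, so few events are expected. A handful of VTE-linked bleeds, or a change of window, could then alter the size or even the sign of the safety difference. The Discussion says the trial is meant to support guidelines, so readers will want to know what prophylaxis itself does to bleeding.

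**Working it through.** **Inputs.** The Sample size calculation section states: "Power calculations were based on an estimated symptomatic VTE incidence of 10% based on the previous DCOG ALL-10 study". It adds "an estimated relative risk reduction (RRR) of 75% based on the abovementioned cohort studies with LMWH in childhood ALL", with 162 per arm, 80% power and two-sided α = 0.05. The arm A risk is therefore 0.10 × (1 − 0.75) = 0.025.

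**The plan's own figure.** The uncorrected two-proportion formula with pooled variance under the null gives 163 per arm after rounding up, and the unpooled form gives 160. Power at 162 per arm is 79.9%. The stated 162 is reproduced to within one patient.

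**Expected VTEs.** Arm B: 162 × 0.10 = 16.2. Arm A: 162 × 0.025 = 4.05. The ratio is 4.0.

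**Randomization-based window.** Let q be the share of VTEs that lead to a qualifying bleed, equal in both arms. The documents give no value, so q is an assumption. The arm B surplus is 162 × q × (0.10 − 0.025) = 12.15q children, or 7.5q percentage points.

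- q = 10%: 1.62 against 0.41 bleeds, surplus 1.2 (0.75 points)
- q = 20%: 3.24 against 0.81, surplus 2.4 (1.5 points)
- q = 40%: 6.48 against 1.62, surplus 4.9 (3.0 points)

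To see the effect on the comparison, assume a 2% background bleeding risk in both arms and a true prophylaxis excess e. The arm A risk is then 0.02 + e + 0.025q and the arm B risk is 0.02 + 0.10q. Power is by exact enumeration of the uncorrected chi-square test with 162 per arm.

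| q | A − B, true e = 5 points | Power | A − B, true e = 3 points | Power |
|---|---|---|---|---|
| 0 | 5.0 | 60.5% | 3.0 | 30.3% |
| 10% | 4.25 | 41.1% | 2.25 | 16.9% |
| 20% | 3.5 | 26.5% | 1.5 | 9.4% |
| 40% | 2.0 | 10.4% | 0.0 | 4.8% |

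**On-LMWH window.** Take the same 2% background and no true excess. If LMWH means study prophylaxis, arm B has no counted time, so its rate is 0% against 2% in arm A. The chi-square test would call that spurious difference significant about 41% of the time. If LMWH also covers treatment of a VTE, and every VTE-linked bleed occurs on LMWH, arm A shows 0.02 + 0.025q and arm B shows 0.10q:

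- q = 10%: 2.25% against 1.0%
- q = 20%: 2.5% against 2.0%
- q = 40%: 3.0% against 4.0%

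The direction of the bias therefore depends on the window and on q.

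**The case against.** The strongest reply is that counting all bleeds by randomized arm is a valid net-safety comparison. A bleed avoided because a VTE was avoided is part of the effect of a prophylaxis policy. The cause-blind definition follows the published criteria that the article cites, and a supportive analysis could properly be left to a statistical analysis plan. This stands. The all-bleed intention-to-treat count should remain, and the absence of a supportive analysis would not be a fault by itself. It does not answer the window problem, because the article itself states both windows and leaves them unreconciled.

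A reader might infer that the on-LMWH sentence itself counts a haemorrhagic sinus thrombosis in a control child. It does not, because that child is not on LMWH at presentation. Such an event enters only through the randomization-based window together with Definitions. Nor does the sentence clearly reach bleeds on treatment for a VTE. The article uses LMWH mainly for the study intervention and calls treatment of a VTE therapeutic anticoagulation, so study prophylaxis is the more natural reading.

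Power is also modest without any VTE-linked bleeds: 30.3% for a 3-point excess. Many small excesses would be missed in any case.

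**Conclusion.** The point holds in limited form. Two bleeding windows are stated and not reconciled, and one is undefined for untreated controls. Under the other, bleeds linked to a VTE are primary safety events and, at the planned effect, would fall mainly in arm B. The surplus is about 1 to 5 children (0.75–3.0 points) for q of 10–40%, which could dilute or hide a prophylaxis excess of that size.

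This rests on the planned 10% and 2.5% risks, on equal bleeding risk per VTE in the two arms, and on an assumed q. It also takes all planned VTEs and their bleeds to fall inside the window; bleeds after the 14- or 7-day cut-off would not count.

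Three stronger conclusions are tempting but unsupported:

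- **Four times as many bleeds in arm B.** The 4:1 figure is a planning ratio of VTEs. It carries over to bleeds only if the risk per VTE is equal, and the documents give no such risk.
- **A precise masked share based on sinus thrombosis.** The 35–43% in the Background does not say whether it covers sinus thrombosis, catheter-related thrombosis or both. The haemorrhagic share is not given.
- **The plan is biased in favour of LMWH.** If the on-LMWH window governs, bleeding on LMWH can be overstated instead.

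**What to change.** In Statistical analysis:

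1. State one bleeding window, starting at randomization and applying to both arms. Keep the all-bleed intention-to-treat comparison in that window as the primary safety analysis.
2. State that any supplementary on-treatment count refers to study prophylaxis. Changing that wording alone is not enough, because arm B would still have no window under that rule.
3. Pre-specify a supportive comparison, in both arms, of bleeds from randomization to the first VTE or the start of therapeutic anticoagulation, with VTE as a competing event.
4. Tabulate by arm the bleeds that occur at or after a VTE, and interpret the two analyses together.
5. Reconcile the outcome itself. Aim and study design names major bleeding alone as the primary safety endpoint, while Statistical analysis adds clinically relevant non-major bleeding.

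The cost is a few sentences. VTEs are already recorded prospectively on dedicated forms, and bleeding is already a study outcome. The drawback is that the supportive analysis ends follow-up at a post-randomization event that treatment affects. It can help explain the intention-to-treat result but cannot replace it, and it should not be the only basis for a statement on bleeding caused by prophylaxis.
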